### **2.4. Population**

This is an open-label study is intended to obtain preliminary estimates in healthy adults of the efficacy and safety of the combination medication. Based on the observational trials in high risk individuals exposed to routine COVID-19 positive contacts frequency of SARS-CoV infection confirmed by RT-PCR is 11.1% (García I.S. et al., 2020). We expect that the investigated pre-exposure prophylaxis allows to eliminate SARS-CoV-2 positive cases to 3% or less during observational period. With Alpha error rate of 0.05, beta error 0.85, we need to include 96 subjects.

Rare adverse events (AEs) are not demonstrable in a clinical study of this size. With the assumption that all enrolled subjects will likely complete the treatment and safety visits in this relatively short duration study, the following statistical considerations apply. With 100 subjects in the treatment group, the chance of observing at least one AE of probability 5% or more is approximately 95%. Therefore, if no AEs of a given type occur, we can be relatively confident that they will occur in fewer than 5% of people.

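### Section 2.4 understates the chance of seeing a 5% adverse event: with 100 subjects it is about 99%, not 95%. The error is conservative and takes one sentence to fix.

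*Protocol*

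**What the plan says.** Section 2.4 of the protocol (Population) first sizes the study on the infection endpoint and concludes that "we need to include 96 subjects". The next paragraph turns to safety. It grants that a study of this size cannot show rare events, and sets its premise: "With the assumption that all enrolled subjects will likely complete the treatment and safety visits". It then gives the detection figure: "With 100 subjects in the treatment group, the chance of observing at least one AE of probability 5% or more is approximately 95" per cent. From that it draws a conclusion for events that are never seen: "if no AEs of a given type occur, we can be relatively confident that they will occur in fewer than 5% of people".

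No confidence level is attached to that last conclusion, but it is presented as following from the detection figure. Nothing else in the protocol says how precisely the study can estimate adverse-event rates. Section 5.2 and the statistical analysis section (Section 6) provide for adverse events to be reported by frequency, intensity and relationship to the medication, without a bound or threshold.

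**The concern.** Sample size, true rate and detection probability are tied by one formula, so any two of them fix the third. The protocol states all three, and they disagree. The safety paragraph also counts 100 subjects where the paragraph before it plans 96, without explaining the difference.

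Safety is half of the objective in Section 2.1 and one of the two endpoints in Section 2.2. The protocol also says of each component that no data exist on giving it by inhalation. A reader who wants to know what an absence of some event type would mean has only this sentence to go on, and would pair the 5% rate with a confidence level that does not belong to it.

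**Working it through.** **Inputs**, all from Section 2.4:

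- n = 100 subjects in the safety statement, and n = 96 as the planned size;
- true event rate 5%, the least favourable case of a rate of 5% or more;
- stated detection probability about 95%;
- no loss to follow-up, as the section assumes.

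**Attempt to reproduce the stated figure.** With independent subjects, P(at least one event) = 1 − (1 − p)^n.

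- n = 100, p = 0.05: 1 − 0.95^100 = 0.9941, or 99.4%.
- n = 96, p = 0.05: 1 − 0.95^96 = 0.9927, or 99.3%.
- Poisson approximation, n = 100: 1 − exp(−5) = 0.9933, or 99.3%.

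The stated 95% is not reproduced. It is 4.4 percentage points below the exact value at n = 100.

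**What a 95% chance would correspond to.**

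- Number of subjects needed at a 5% rate: ln(0.05)/ln(0.95) = 58.4, so 59.
- Rate detectable with n = 100: 1 − 0.05^(1/100) = 0.0295, about 3%. At exactly 3%, 1 − 0.97^100 = 95.2%.
- Rate detectable with n = 96: 1 − 0.05^(1/96) = 0.0307, about 3.1%. At exactly 3%, 1 − 0.97^96 = 94.6%.

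**Upper limit for the rate after zero events.**

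| n | one-sided 95%: 1 − 0.05^(1/n) | two-sided 95%, upper end: 1 − 0.025^(1/n) | confidence that the rate is below 5%: 1 − 0.95^n |
|---|---|---|---|
| 100 | 2.95% | 3.6% | 99.4% |
| 96 | 3.07% | 3.8% | 99.3% |

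The rule of three (3/n) gives 3.0% for 100 subjects.

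**Other readings tried.**

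- Loss to follow-up: bringing 100 subjects down to the 59 that give 95% takes a 41% loss, which contradicts the stated assumption of completion.
- At least two events instead of one: 96.3% for n = 100, but the text says at least one.
- Two arms sharing the 100: Section 2.3 describes a single open-label cohort, so there is no split.

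**The case against.** The strongest defence concerns consequence, since the arithmetic itself cannot be defended. The mistake understates what the study can detect, so anyone relying on the sentence would claim less about safety than the data support. No sample size, endpoint, safety rule or analysis in the protocol uses the figure. All of this stands, and it makes the point a minor correction.

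A reader might go further and infer that the 5% bound is itself wrong and has to become 3%. The documents do not support that. The conclusion claims only relative confidence, with no level given, and after zero events a rate below 5% holds with about 99% confidence at either sample size. The false figure is the 95% in the sentence before it. Quoting 3% is one valid repair; keeping 5% and quoting about 99% is another.

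A reader might also count the 100 against 96 as a second defect of weight. The figures differ without explanation and should agree, but 100 can be read as a round illustrative number, and the effect is about 0.1 percentage point (99.4% against 99.3%; 2.95% against 3.07%).

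A last caution bears on the repair. A tight limit leaves less room for incomplete follow-up than a loose one, and Section 2.7.1 takes volunteers out of the study once they test positive. As an illustration only, suppose the share not fully observed equalled the 11.1% background infection rate in Section 2.4, which leaves about 85 of 96. Detection at a 5% rate would then be 98.7% and the one-sided zero-event limit 3.5%. This does not rescue the stated 95%, and Section 6 keeps the data of all enrolled volunteers in the analysis. It is a reason to say that the limit refers to fully observed subjects.

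**Conclusion.** The detection figure is wrong as written. With 100 subjects and a 5% rate the chance of at least one event is 99.4%, and with the planned 96 it is 99.3%. A 95% chance corresponds to a true rate of about 3%. The result rests on independent subjects, complete observation as the section assumes, and the exact binomial formula; the Poisson approximation does not change it.

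The size is small and the direction conservative. The conclusion drawn after zero events is true but looser than a 95% level implies, and neither the design nor the primary endpoint depends on it. The reason to correct it is that it is the protocol's only statement of safety precision.

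**What to change.** Either of two repairs is valid.

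- **Minimal:** keep the 5% rate and the conclusion drawn from it, and change the detection probability from about 95% to about 99%.
- **Fuller, and preferable because it also aligns the subject number:** replace the statement with wording such as:

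> With 96 subjects, the chance of observing at least one AE of true probability 5% is about 99%, and of 3% about 95%. If no AE of a given type occurs among 96 fully observed subjects, the one-sided 95% upper confidence limit for its rate is about 3.1% (3.8% as the upper end of a two-sided 95% interval).

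Whichever is chosen, use the planned 96 or explain why the safety paragraph counts 100, and label any quoted limit as one-sided or two-sided. The cost is an edit of one or two sentences in Section 2.4. No procedure, visit, endpoint or sample size changes.

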### **2.5. Inclusion Criteria**

- 2.5.1. Healthy volunteers aged between 18 and 80 years;
- 2.5.2. Informed consent to participate in the study signed by a healthy volunteer;
- 2.5.3. An ability to cooperate adequately (the volunteer can understand the information provided about the study and is willing to comply with the requirements of the study protocol);

### **2.6. Exclusion Criteria**

Healthy volunteers cannot be included in the trial if they meet at least one of the following criteria.

2.6.1. Criteria related to the disease:

Detection of SARS-CoV-2 virus RNA by polymerase chain reaction (PCR) in biomaterial samples and/or positive enzyme-linked immunosorbent assay ELISA IgM and ELISA IgG to the virus in a healthy volunteer;

2.6.2. Criteria related to the combination medication, previous therapy and concomitant therapy:

Hypersensitivity or individual intolerance to the components of the combination therapy according to the medical history.

2.6.3. Criteria related to the concomitant pathology:

According to the medical history and physical examination:

- any diseases or conditions that, in opinion of the investigator, would make it difficult to interpret the results of treatment or may limit the participation of a healthy volunteer in the study.

According to screening laboratory tests:

- related to the compliance of healthy volunteers in the study;
- any diseases or conditions that, in opinion of the investigator, would make it difficult to interpret the results of treatment or may limit the participation of healthy volunteers in the study;

Healthy volunteers who, in the opinion of the investigator, are obviously or likely unable to understand and evaluate the information regarding this study within the process of signing the informed consent form, in particular regarding the expected risks and possible discomfort.

The inability or unwillingness of a healthy volunteer to follow the rules for carrying out the study and participating in a clinical trial.

2.7. **Early Discontinuation Criteria**

2.7.1. A healthy volunteer will be excluded from the study if SARS-CoV-2 virus RNA is detected in biomaterial samples by a polymerase chain reaction (PCR) for COVID-19 or if enzyme-linked immunosorbent assay (ELISA) IgM and ELISA IgG results are positive.

2.7.2. A healthy volunteer may withdraw their consent to participate in the study at any time and without giving reasons. The investigator may also decide on early discontinuation of the participation of a healthy volunteer in the study at any time if the patient's condition requires it.

2.7.3. Main reasons for early discontinuation of participation of a healthy volunteer in the study:

Individual intolerance to the combination medication or any of its components;

Failure to meet the inclusion and exclusion criteria;

Refusal of a healthy volunteer to participate in the study or the withdrawal of informed consent by a healthy volunteer;

Development of adverse events that prevent further prophylactic therapy with the medication;

The emergence of a serious adverse event in a healthy volunteer;

The emergence of exclusion criteria in the course of the study;

Any condition of a healthy volunteer that requires, in the opinion of the investigator, the withdrawal of the patient from the study;

Discontinuation of the trial by the research center, investigator, or regulatory authority.

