**There are no data on the inhaled administration of the drug.**

**Manufacturers - owners of the registration license:**

GROTEX OOO (Russia), SINTEZ OAO (Russia), BINNOFARM AO (Russia) and others.

VIDAL 22.04.2020 [https://www.vidal.ru/drugs/potassium\\_chloride\\_\\_44667](https://www.vidal.ru/drugs/potassium_chloride__44667)

**INN:** INOSINE GLYCYL-CYSTEINYL- GLUTAMATE DISODIUM

**Brand names of pharmaceuticals:** Molixan®

**Therapeutic classification:** metabolic agent

**ATC code:** V03AX Other therapeutic products

**Composition and pharmaceutical form:** solution for intravenous and intramuscular administration; 1 ml of a 3% solution for injections contains inosine glycyL-cysteinyL-disodium glutamate - 30 mg; in ampules of 1 and 2 ml with a break ring or dot; 5 or 10 ampules in a blister pack, 1 blister in a cardboard box.

One milliliter of the solution contains the following:

Active substance: inosine glycyL-cysteinyL-disodium glutamate 30 mg.

Excipients: sodium acetate trihydrate 13.6 mg, diluted acetic acid up to pH 6.0, and water for injections up to 1 ml.

**Pharmacological effect:** antiviral, immunomodulatory, hepatoprotective.

**Mechanism of action:** regulates the thiol-disulfide exchange of epithelial and immunocompetent cells, the production of cytokines by macrophages, including interleukin-2,  $\alpha$ - and  $\gamma$ -interferons, inhibits the cytolysis of functionally active cells and induces apoptosis of virus-infected cells.

**Contraindications:** individual hypersensitivity, pregnancy, breastfeeding.

**Side effects:** uncommon - increased body temperature (up to 37.1–37.5°C), slight soreness at the injection site.

**Registered administration and dose:** iv, i/m for lasting and severe forms of acute viral hepatitis B: 10–30 mg/day daily, single-dose, duration of the course: 24 days (in combination with symptomatic and detoxification therapy). In the case of chronic viral hepatitis B: 10–30 mg/day, daily, single-dose, for 3 months or more (combination with antiviral chemotherapy is possible). In the case of chronic viral hepatitis C: 30–60 mg/day in 1-2 doses, treatment duration 3-6 months (in combination with antiviral chemotherapy).

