## 8. APPENDICES

### Appendix 1

|                                                                   | Study Plan |           |           |   |    |           |
|-------------------------------------------------------------------|------------|-----------|-----------|---|----|-----------|
|                                                                   | Procedures | Screening | Treatment |   |    | Follow-up |
|                                                                   | Visit      | 0         | 1         | 2 | 3  | 3 4       |
|                                                                   | Days       | -2 - 0    | 1         | 7 | 14 | 21±1 28±1 |
| Informed Consent                                                  |            | X         | -         | - | -  | -         |
| Insurance                                                         |            | X         |           |   |    |           |
| PCR for SARS-CoV-2 RNA                                            |            | X         | X         | X | X  | X         |
| ELISA IgM and IgG to SARS-CoV-2                                   |            | X         | -         | - | -  | X         |
| Demographics, Complaints and Medical History, Anthropometric Data |            | X         | X         | - | -  | -         |
| Inclusion and Exclusion Criteria Assessment                       |            | X         | X         | X | X  | X         |
| Physical Examination                                              |            | X         | X         | X | X  | X         |
| Vital Signs Assessment (BP, HR, RR, TEMP)                         |            | -         | X         | X | X  | X         |
| Exclusion Criteria Assessment                                     |            | X         | -         | - | -  | -         |
| Previous Therapy Assessment                                       |            | X         | X         | X | X  | X         |
| Concomitant Therapy Assessment                                    |            | X         | X         | X | X  | X         |

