#### Medical history:

Cardiovascular diseases: **YES/NO**

If yes, specify \_\_\_\_\_

Treatment for cardiovascular diseases: **YES/NO**

If yes, specify which medications and in what dose are taken daily \_\_\_\_\_

Pulmonary diseases: **YES/NO**

If yes, specify \_\_\_\_\_

Treatment for pulmonary diseases: **YES/NO**

If yes, specify which medications and in what dose are they taken daily \_\_\_\_\_

Gastrointestinal diseases: **YES/NO**

If yes, specify \_\_\_\_\_

Treatment for gastrointestinal diseases: **YES/NO**

If yes, specify which medications and in what dose are they taken daily \_\_\_\_\_

Musculoskeletal system diseases: **YES/NO**

If yes, specify \_\_\_\_\_

Treatment for musculoskeletal system diseases: **YES/NO**

If yes, specify which medications and in what dose are they taken daily \_\_\_\_\_

Diabetes: **YES/NO**

Treatment for diabetes: **YES/NO**

If yes, specify which medications and in what dose are they taken daily \_\_\_\_\_

Acute respiratory viral infections or influenza in the last 3 months: **YES/NO**

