**Exclusion criteria**

Healthy volunteers cannot be included in the trial if they meet at least one of the following criteria.

Criteria related to the underlying disease:

Detection of SARS-CoV-2 virus RNA by polymerase chain reaction (PCR) for COVID-19 in biomaterial samples and positive reactivity of enzyme-linked immunosorbent assay (ELISA) IgM and ELISA IgG to the virus in a healthy volunteer: **YES/NO**

Criteria related to the combination medication, previous therapy and concomitant therapy: **YES/NO**

Hypersensitivity or individual intolerance to the components of the combination medication products according to the medical history: **YES/NO**

Criteria related to the concomitant pathology:

According to the medical history and physical examination: **YES/NO**

Any diseases or conditions that, in opinion of the investigator, make it difficult to interpret the results of treatment or may limit the participation of a healthy volunteer in the study: **YES/NO**

According to screening laboratory tests:

Related to the compliance of healthy volunteers in the study: **YES/NO**

Any other diseases or conditions that, in the opinion of the investigator, would make it difficult to interpret the results of treatment or may limit the participation of a healthy volunteer in the study: **YES/NO**

Healthy volunteers who, in the opinion of the investigator, are obviously or likely unable to understand and evaluate the information regarding this study within the process of signing the informed consent form, in particular, regarding the expected risks and possible discomfort: **YES/NO**

The inability or unwillingness of a healthy volunteer to follow the rules for carrying out the study and participating in a clinical trial: **YES/NO**

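### Pregnancy and breastfeeding are contraindications in the protocol's own product text but are not named exclusions

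*Protocol*

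**What the plan says.** The Description of the Combination Medication gives the contraindications of the inosine component as "individual hypersensitivity, pregnancy, breastfeeding".

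Section 2.5 admits "Healthy volunteers aged between 18 and 80 years" who consent and can cooperate. It sets no condition on sex, child-bearing potential or contraception.

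Section 2.6.2, on criteria related to the medication and to previous and concomitant therapy, has a single entry: "Hypersensitivity or individual intolerance to the components of the combination therapy according to the medical history". The exclusion checklists for Visit 0 and Visit 1 in the Individual Record Form repeat it as "Hypersensitivity or individual intolerance to the components of the combination medication products according to the medical history".

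Section 2.6.3, on concomitant pathology, adds a discretionary clause covering "any diseases or conditions that, in opinion of the investigator, would make it difficult to interpret the results of treatment", or that may restrict the volunteer's participation.

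Section 2.7.3 lists among the reasons for discontinuation "The emergence of exclusion criteria in the course of the study". The same item appears on the forms for Visits 1 to 4.

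**The concern.** The section meant for product-related exclusions drops two of the three contraindications that the same protocol prints for one of its two components. Neither is an illness, so the healthy-volunteer requirement does not remove such people. If the investigator does not ask, or does not read 2.6.3 as covering pregnancy and breastfeeding, the volunteer meets every written criterion and is dosed.

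The stakes are participant safety in a prophylaxis study of healthy people. The daily inosine dose exceeds any registered dose quoted in the protocol, and the route is one for which the protocol says there are no data. The protocol counts a congenital anomaly or birth defect as a serious adverse event, but event registration stops when participation ends, at most 30 days after it starts. The study could not observe that outcome in a pregnancy exposed during treatment, so the practical control is at entry.

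**Working it through.** The protocol states no figure on this point, so the check sets its own texts side by side.

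**1. Contraindications against named exclusions**

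| Contraindication of the inosine component | Section 2.6.2 | Visit 0 checklist | Visit 1 checklist |
|---|---|---|---|
| Hypersensitivity | named | named | named |
| Pregnancy | not named | not named | not named |
| Breastfeeding | not named | not named | not named |

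Of 3 contraindications, 1 is named in all three places and 2 are named in none.

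**2. Whether another criterion removes these volunteers.** Section 2.5 does not: a pregnant or breastfeeding adult can be healthy, aged 18 to 80, consenting and cooperative. In 2.6 the only candidate is the 2.6.3 clause, which depends on the investigator's opinion and sits under concomitant pathology.

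**3. Whether the investigator would have the information.** The yes/no items in the Visit 0 medical-history block, as shown, are cardiovascular 2, pulmonary 2, gastrointestinal 2, musculoskeletal 2, diabetes 2, and "Acute respiratory viral infections or influenza in the last 3 months" 1. That is 2 + 2 + 2 + 2 + 2 + 1 = 11 items over 6 topics, none on pregnancy or breastfeeding. The only laboratory tests in the Appendix 1 Study Plan are SARS-CoV-2 PCR and ELISA. This step is supporting evidence only, because the form may be incomplete in the copy at hand.

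**4. The stop rule.** The emergence rule appears in 5 places: section 2.7.3 and the forms for Visits 1, 2, 3 and 4. It works through the list of exclusion criteria. Pregnancy is not on that list, so a pregnancy found during the 14 treatment days does not clearly trigger it.

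**5. Exposure.** The daily preparation uses 4.0 ml of a 3% solution (30 mg/ml): 4.0 × 30 = 120 mg/day, which agrees with the daily dose in the Instruction for Use. The highest registered dose quoted in the product text is 60 mg/day by injection, and 120 / 60 = 2. The study dose is therefore twice that maximum, by an inhaled route for which the protocol reports no data. Nothing here gives a reason to relax the stated contraindications.

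**The case against.** The strongest reply is that this is a lack of specificity and not a permission. No text invites pregnant or breastfeeding volunteers, the 2.6.3 clause reaches conditions as well as diseases, and the contraindication is printed in the document the investigator works from. That is fair as far as it goes: discretionary cover exists at entry. But nothing obliges an investigator to use it.

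Discretionary cover also exists after entry. Section 2.7.2 lets the investigator end participation when the volunteer's condition calls for it, and 2.7.3 and the forms for Visits 1 to 4 list any condition that the investigator judges to require withdrawal. These are real routes for a pregnancy found on treatment, but they too depend on opinion.

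The record-form evidence is weak. Appendix 1 schedules "Demographics, Complaints and Medical History, Anthropometric Data" at screening, yet the Visit 0 form as shown has no age or sex field. Appendix 1 also schedules a day 28 visit, but the forms shown end at day 21. Pages may be missing, and the consent form cannot be checked. This objection stands against the 11-item count. It does not affect section 2.6.2 or the two checklists, which are visible.

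Two further remarks are right. A criterion added only at Visits 0 and 1 puts no pregnancy question on the later forms. And the contraindications of potassium chloride (impaired renal function, complete heart block) are not named either. Those are diseases, which healthy-volunteer status and 2.6.3 catch more naturally, so that gap is smaller.

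**Conclusion.** The point holds. Two of the three contraindications that the protocol states for its inosine component are not named exclusions in section 2.6.2 or in either eligibility checklist, and rest on investigator opinion both at entry and at withdrawal. Eligibility belongs in the protocol, so this is not a detail to leave to a statistical analysis plan.

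The conclusion rests on section 2.6.2, the two checklists and the product text, and does not depend on any page that may be missing. How many volunteers would be affected cannot be estimated from the protocol. No endpoint, sample size or error rate changes. It should be corrected as a participant-safety matter, but because discretionary cover exists it does not make the plan unusable.

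**What to change.** Add to section 2.6.2: *Pregnancy or breastfeeding, according to the medical history.* Add two matching YES/NO lines, one for each condition, to the Visit 0 and Visit 1 exclusion checklists.

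The emergence rule in 2.7.3 and on the forms for Visits 1 to 4 then applies to both conditions without redrafting. Appendix 1 already schedules an assessment of inclusion and exclusion criteria at the later visits, which is where a new pregnancy would be picked up. A prompt on those later forms would make that more reliable.

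A history question will not find an unrecognised early pregnancy. A urine test at screening is the optional stronger step. The contraindications of potassium chloride could be named in the same edit.

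The cost is one line in 2.6.2 and two tick-box lines in each of two forms (four lines in all), with a few more volunteers excluded.

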### **2.2. Endpoints**

- 3.2.1 Determine the frequency of laboratory confirmed SARS-CoV-2 cases, defined by RT-PCR positivity within 28 days observational period, in high risk population with routine COVID-19 positive contacts.
- 3.2.2 Evaluation of the safety of aerosol combination therapy as the pre-exposure prophylaxis for COVID-19.

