#### 5.2.2. Adverse events registration and reporting

##### Adverse events (AE)

The protocol requires the registration of all AEs that occur in the patient during and after administration of the medicinal product and until the end of the patient's participation in the trial.

An adverse event is defined as “any untoward medical occurrence in a patient in a clinical investigation who received a medicinal product; the event does not necessarily have to have a causal relationship with this treatment” (National Standard of the Russian Federation GOST R52379-2005 “Good Clinical Practice”).

An AE can be any symptom (including a clinically significant deviation of the laboratory measurement from the reference values), complaint, or disease, the time of occurrence of which does not exclude a causal relationship with the use of the investigational medicinal product, regardless of the existence of such a relationship.

AEs are classified by severity (nonserious or serious AEs), causal relationship with the investigational medicinal product (no/yes; if yes: probable, possible, unlikely, conditional, unclassifiable), and intensity (mild, moderate, severe).

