## 6. STATISTICAL ANALYSIS

The methods for statistical analysis of the obtained data are determined by the nature, type, and distribution of the data. The applicability of a number of statistical methods will be evaluated upon the completion of the data collection due to the unknown distribution, sample uniformity, etc. In the course of the analysis, the list of methods used can be expanded if necessary for high-quality data processing.

Statistical processing of data obtained in the study will be carried out using statistical programs or other special software that would ensure high quality of the results. Interval (quantitative) data will be described using the arithmetic mean, standard deviation, median, lower (25%) and upper (75%) quartiles, minimum and maximum values. Categorical (qualitative) data will be described using absolute and relative frequencies. To compare normally distributed quantitative data, standard parametric criteria shall be employed: Student's t-test for dependent/independent samples and analysis of variance (ANOVA) for repeated measurements. For the comparison of quantitative data that are not normally distributed, standard nonparametric tests shall be employed. The frequencies of the variables will be compared between the groups using Pearson's  $\chi^2$  test or Fisher's exact test.

AEs will be analyzed based on the frequency of adverse events/serious adverse events. Adverse events registered within the study will be presented by incidence rate (the number of patients with AEs and the number of such AEs in the group). AEs will also be presented by their intensity and relationship with the administration of the combined medicinal product.

Regardless of the reason for the termination of the study, the data of all enrolled healthy volunteers will be taken into account when analyzing the efficiency and safety of the investigational therapy.

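### Section 2.7 ends participation in the study, not only treatment, at infection or a serious adverse event, so scheduled safety visits, new adverse events and some endpoint PCRs are lost

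*Protocol*

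**What the plan says.** The efficacy endpoint in section 2.2 is: "Determine the frequency of laboratory confirmed SARS-CoV-2 cases, defined by RT-PCR positivity within 28 days observational period". Section 5.1 repeats that infection is confirmed by PCR. Safety is the second endpoint.

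Section 2.7.1 sets the exit rule: "A healthy volunteer will be excluded from the study if SARS-CoV-2 virus RNA is detected in biomaterial samples by a polymerase chain reaction (PCR"). The same sentence applies it to positive ELISA IgM and IgG. The exit is from the study, and it is worded as mandatory. Section 2.7.3 lists the main reasons for ending participation early. They include intolerance, adverse events that prevent further prophylaxis, and "The emergence of a serious adverse event in a healthy volunteer".

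Section 5.2.2 requires adverse events to be registered "until the end of the patient's participation in the trial". Section 5.2.1 has them assessed at each visit and around each administration. No section provides visits for a volunteer who has left.

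Three other provisions matter here:
- Section 5.2.2, on reporting, requires the outcome of a registered adverse event to be recorded and later information about it to be added.
- Section 6 says that "the data of all enrolled healthy volunteers will be taken into account when analyzing the efficiency and safety".
- Section 2.4 assumes that all enrolled volunteers are likely to complete treatment and the safety visits.

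Appendix 1 schedules PCR at every visit and "ELISA IgM and IgG to SARS-CoV-2" at screening and in follow-up.

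**The concern.** The reason for stopping observation is the very outcome the study wants to learn about. A volunteer with a breakthrough infection or a serious adverse event is among those in whom later safety information is most useful. The protocol's own product descriptions say that no data exist on inhaled administration of either component.

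Four things are at stake:
- New adverse events after exit fall outside the registration window.
- The remaining scheduled examinations do not take place.
- A volunteer who leaves for an adverse event, not yet infected, has no further PCR, so the 28-day endpoint is not observed for that person.
- A volunteer who is seropositive but PCR-negative meets an exit rule based on infection, yet is not an event under the RT-PCR endpoint.

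None of this can be recovered in the analysis, because the data would not have been collected.

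**Working it through.** **1. The plan's sample size.** Inputs from section 2.4: reference rate p0 = 0.111, expected rate p1 = 0.03, alpha 0.05, and "beta error 0.85, we need to include 96 subjects". Reading 0.85 as power and alpha as two-sided, a one-sample test of a proportion gives

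n = [(z₀.₉₇₅·√(p0(1−p0)) + z₀.₈₅·√(p1(1−p1))) / (p0−p1)]²
= [(1.960 × 0.3141 + 1.036 × 0.1706) / 0.081]² ≈ 95.7, so 96.

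The figure reproduces. It is used below only as the cohort size, and it contains no allowance for volunteers leaving.

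**2. Expected exits on PCR alone.**
- At 3%: 96 × 0.03 = 2.9, about 3 volunteers.
- At 11.1%: 96 × 0.111 = 10.7, about 11 volunteers.

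These are the protocol's own two rates, so the range needs no outside assumption. It covers every volunteer found infected by PCR.

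**3. Visits lost per exit.** Appendix 1 has visits on Days 1, 7, 14, 21 and 28.

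| First positive PCR | Scheduled visits lost |
|---|---|
| Day 7 | 3 (Days 14, 21, 28) |
| Day 14 | 2 (Days 21, 28) |
| Day 21 | 1 (Day 28) |
| Day 28 | 0 |

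The 3 to 11 is therefore an upper bound on the expected number who lose a visit.

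**4. Exits for adverse events.** The documents give no expected number. For each such exit, the unobserved part of the endpoint window follows from the day of leaving. An exit at Day 7 leaves 28 − 7 = 21 of 28 days (75%) without PCR, and an exit at Day 14 leaves 14 of 28 (50%).

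**5. The provisions side by side.** Section 2.4 builds its safety reasoning on near-complete attendance. Section 2.7 guarantees incomplete attendance for infected volunteers unless they are first positive at the last visit, and allows it for those with serious events. Section 6 retains whatever was collected, so a PCR-positive volunteer remains a counted case. It cannot supply visits that were not held.

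**6. Serology.** Section 2.7.1 and the record forms for Visits 1 and 2 make exit depend on IgM and IgG together. The forms for Visits 3 and 4 say and/or, so one antibody is enough. The trigger therefore changes during the study. ELISA is scheduled only at screening and in follow-up, so a serological exit costs little follow-up time. Its effect is on the infection count. With 3 PCR cases and m seropositive, PCR-negative volunteers (m is an assumption), the supplementary count would be:

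| m | PCR only | PCR plus serology |
|---|---|---|
| 0 | 3/96 = 3.1% | 3/96 = 3.1% |
| 1 | 3.1% | 4/96 = 4.2% |
| 2 | 3.1% | 5/96 = 5.2% |
| 4 | 3.1% | 7/96 = 7.3% |

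**The case against.** The best defence is that this is a pilot cohort seeking preliminary estimates, that the primary event is counted before the volunteer leaves, and that section 6 uses everyone's data. All of that is correct, and the numerator of the RT-PCR endpoint is intact for those who leave on PCR positivity. Also, only 2.7.1 is worded as mandatory. The adverse-event items in 2.7.3 are a list of main reasons. None of this restores the later visits or brings new adverse events back inside the registration window.

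Four stronger readings are tempting, and the document does not support them.

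- *Outcomes of serious events go unrecorded.* Section 5.2.2 requires outcome and resolution to be registered and later information to be added to the existing form. What is lost is scheduled follow-up and new events.
- *Volunteers without later PCR are scored as uninfected.* Section 6 does not say so. How missing PCR results are handled commonly belongs to the statistical analysis plan, which is not shown.
- *Infections missed by weekly PCR inflate the chance of a falsely favourable result.* The 11.1% reference is itself RT-PCR confirmed, so discounting only the study's rate is not like for like. Missed infections would also be missed without any exit rule, and section 6 states no test against 11.1%.
- *No record form can hold an ELISA result.* The forms available end at Visit 4 (Day 21), and Day 28 is not among them. The visible forms do carry a yes/no item on ELISA reactivity.

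It is also fair to say that an RT-PCR-only endpoint is stated consistently and matches the reference rate. That is why serology is suggested as a supplementary count and not as a change of endpoint.

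**Conclusion.** The concern holds in a limited form and should be fixed. Section 2.7 merges ending treatment with ending the study, and section 5.2.2 then closes adverse-event registration. Up to about 3 (at 3%) to 11 (at 11.1%) of 96 volunteers lose remaining visits and registration of new adverse events after PCR positivity. An unstated number who leave for adverse events lose the same, and also lose later PCR for the 28-day endpoint. This contradicts the completion assumption in section 2.4.

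The range rests only on the protocol's two infection rates and its sample size of 96. The number leaving for adverse events and the number seropositive but PCR-negative cannot be derived from the document. The RT-PCR case count is not invalidated, and no bias of known size in the infection rate is shown.

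**What to change.** In section 2.7 and the matching items on the record forms, separate ending study treatment from ending participation. State that a volunteer who meets a criterion in 2.7.1, or who stops for intolerance, an adverse event or a serious adverse event, stays in the scheduled follow-up to Day 28 unless consent is withdrawn. Adverse-event recording continues throughout, and the remaining PCRs continue for those not yet positive. What happens to treatment in each case is a clinical rule for the sponsor and is not addressed here.

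Reconcile the serology trigger between section 2.7.1 and Visits 1 and 2 on the one hand, and Visits 3 and 4 on the other. Report volunteers who are seropositive but PCR-negative at the planned follow-up ELISA as a supplementary infection count beside the RT-PCR endpoint, without replacing it.

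The cost is an amendment of wording and a few more completed visits that are already scheduled. Section 2.8 places all visits in a specialized hospital, so infected volunteers would have to be seen there, and the sponsor should confirm that this is workable. The PCR and ELISA are already in Appendix 1.
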